### Study design

2.1

The study is a randomized controlled trial investigating human amniotic membranes as biological wound dressings in the treatment of superficial partial thickness, deep partial thickness or full thickness burn wounds of the upper extremities, the torso or the lower extremities requiring enzymatic debridement. This intervention will be compared to human skin allografts. As a study population all burn patients admitted to our burn unit will be screened at admission. A total of 30 patients will be included in this study. The total duration for an individual patient will be 92 days from the admission to our burn unit to the 3-month postoperative control. See Fig. 1 for the CONSORT-diagram.

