### Study visit 1: Selection of study burn areas/randomization/intervention

4.3

For each patient two 7 × 7cm superficial partial thickness, deep partial thickness or full thickness burn areas with similar burn depths will be compared and allocated to their respective treatment arm by randomization. The randomization will be stratified for wound size. Every patient serves as their own control in the sense that only patients will be included with at least two wounds, of which one wound is treated with amniotic membranes (experimental) and the other wound is treated with allogenic skin graft (standard of care). All other wound area is treated according to the regular standard of care. During study visit 1 the coverage with human amniotic membranes and human skin allografts will take place in coordination with the eye bank. Following points will be part of the first study visit: photographic documentation, assessment of safety parameters, extraction of laboratory and vital parameters.

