### Study visit 2: Autologous skin grafting

4.4

Visit 2 will take place 3–14 days after visit 1. Autologous split thickness skin grafting will be performed according to preexisting standard operating procedures. The skin grafting will be performed in the operating room. Following will be performed additionally: photographic documentation and the assessment of safety parameters.

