### Study visit 3: First dressing change after skin grafting

4.5

Visit 3 will take place 4–6 days after visit 2 and will mark the first dressing change after skin grafting. The dressing change will be performed by the ICU-staff (intensive care unit)/normal ward staff. Following points will be part of the first study visit: photographic documentation, assessment of primary and secondary outcomes, assessment of safety parameters, extraction of laboratory and vital parameters.

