### Study visit 4: Dressing change after 12–14 days after skin grafting

4.6

Visit 4 will take place 12–14 days after visit 2. The dressing change will be performed by the ICU-staff/normal ward staff. Following points will be part of the first study visit: photographic documentation, assessment of primary and secondary outcomes, assessment of safety parameters, extraction of laboratory and vital parameters.

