### Visit 5: 90 days postoperatively ( ± 10 days)

4.7

Visit 5 will take place approximately 90 days ( ± 10 days) after application of the amniotic membrane and the skin allograft have been applied. This study visit will be part of a routine clinical follow up, but these additional study specific documentations will be performed: photographic documentation, assessment of safety parameters and the clinical assessment of the scar formation using the POSAS-Score.

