### Planned analysis

5.4

Data processing including data entry, cleaning and verification, and preparation of data sets for statistical analysis will be performed locally. In order to ensure uttermost objectivity during the analytical stage, the primary and principal secondary analyses will be conducted with concealed intervention allocation for the statistician, which will only be broken once the analysis is finalized.

Time points chosen for statistical inference of the primary endpoint will be the intervention start point defined as visit 1 and the time points visit 3 at 4–6 days and visit 4 at 12–14days after intervention start. Differences on the primary outcome measure between time points and intervention groups will be tested using linear mixed effects model analysis. As independent variable fixed effects, time point and intervention arm will be entered into the model, respectively. Interaction terms will be tested and included if they add to the models informativity. As random effects, intercepts for subjects as well as per-subject random slopes for the effect of time will be employed, if the model does not suffer overfitting from the addition of the latter. P values will be calculated using Satterthwaite's method of approximation.

Population characteristics will be compared using a paired *t*-test – when continuous – and McNemar's test when categorical. A two-sided p < 0.05 was considered statistically significant. Values will be given as means and 95% confidence intervals or counts and (percentages) as appropriate. Statistical analysis will be performed through a fully scripted data management pathway using the R environment for statistical computing.

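### Section 5.4 counts the primary-endpoint visits from dressing application (visit 1), but the visit plan counts the same days from grafting (visit 2), and the two sets of windows never overlap

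*Protocol article*

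**What the plan says.** All references are to the protocol article.

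- **Section 5.4 (Planned analysis)** takes as its anchor "the intervention start point defined as visit 1" and places "visit 3 at 4–6 days and visit 4 at 12–14days after intervention start". It lists visit 1 together with visits 3 and 4 as time points for inference on the primary endpoint. Time point and arm are fixed effects. Interactions and per-subject random slopes for time may be added.
- **Section 4.3** says what visit 1 is: "During study visit 1 the coverage with human amniotic membranes and human skin allografts will take place".
- **Section 4.4**: "Visit 2 will take place 3–14 days after visit 1". Visit 2 is the autologous skin grafting.
- **Section 4.5**: "Visit 3 will take place 4–6 days after visit 2".
- **Section 4.6**: "Visit 4 will take place 12–14 days after visit 2".
- **Section 3.1** defines the primary outcome as percentage skin graft take, assessed at visits 3 and 4.

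On visit 5, section 3.2 and the heading of section 4.7 describe the visit as postoperative, while the body of section 4.7 counts its 90 ± 10 days from the time "after application of the amniotic membrane and the skin allograft have been applied". Section 2.1 states: "The total duration for an individual patient will be 92 days from the admission", ending at a control that it also calls postoperative. Section 2.6 uses the word operation for the autologous grafting.

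**The concern.** The same two day ranges are attached to two different starting events, and those events lie 3 to 14 days apart. This concerns the primary endpoint, and the endpoint exists only after the second event: graft take cannot be assessed until a graft has been placed.

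The definition of time enters the primary model through the fixed effect, the possible interaction and the possible random slope. If a programmer builds analysis windows from section 5.4, assessments made on schedule fall outside them. If time is coded as days since visit 1, observations with the same time value can come from grafts of quite different ages. Either would affect the time effect and any arm-by-time interaction, and the first would also affect which data are used.

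**Working it through.** **Inputs.** Visit 1 is day 0 (5.4). Grafting day g is 3 to 14 (4.4). Visit 3 is k = 4 to 6 days after grafting (4.5). Visit 4 is k = 12 to 14 days after grafting (4.6). Section 5.4 puts the visits at days 4–6 and 12–14 from day 0.

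**1. Visit plan in days from visit 1** (day = g + k)

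| Visit | Visit plan | Section 5.4 | Smallest gap |
|---|---|---|---|
| 3 | 3 + 4 = 7 to 14 + 6 = 20 | 4 to 6 | 7 − 6 = 1 day |
| 4 | 3 + 12 = 15 to 14 + 14 = 28 | 12 to 14 | 15 − 14 = 1 day |

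Each section 5.4 window spans 2 days from first to last. A planned visit could fall inside it only if g were at most 6 − 4 = 2 (visit 3) or 14 − 12 = 2 (visit 4), and the smallest permitted g is 3. Enumerating every whole-day combination of grafting day and visit day gives 0 matches for either visit.

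**2. Section 5.4 windows in days from grafting** (day − g)

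- Visit 3: from 4 − 14 = −10 to 6 − 3 = 3. The planned 4–6 days is never reached.
- Visit 4: from 12 − 14 = −2 to 14 − 3 = 11. The planned 12–14 days is never reached.
- For g = 7 to 14, which is 8 of the 12 permitted grafting days, the whole visit 3 window (days 4–6) lies before grafting.
- At visit 1 (day 0), grafting is still at least 3 days away, so graft take is undefined for every patient.

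**3. Numeric time since visit 1.** Grafting day varies by 14 − 3 = 11 days, so on any given day from visit 1 graft ages can differ by that much. Between two on-schedule assessments the largest difference is 14 − 4 = 10 days. For example, a visit 4 with g = 3 (3 + 14) and a visit 3 with g = 13 (13 + 4) both fall on day 17. Under visit labels, graft age within a visit varies by only 2 days.

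**4. Visit 5 and the 92 days.** Section 4.1 puts visit 1 about 48–96 h, or 2–4 days, after admission.

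| Anchor | Nominal, from admission | With ± 10 days |
|---|---|---|
| Application | 2 + 90 = 92 to 4 + 90 = 94 | 2 + 80 = 82 to 4 + 100 = 104 |
| Grafting | 2 + 3 + 90 = 95 to 4 + 14 + 90 = 108 | 2 + 3 + 80 = 85 to 4 + 14 + 100 = 118 |

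The stated 92 days is reproduced as 2 + 90 under the application anchor. The two windows overlap and both contain day 92. If visit 5 is counted from application, graft age at the scar assessment runs from 80 − 14 = 66 to 100 − 3 = 97 days.

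**5. Sample size.** The calculation in section 5.2 uses no visit timing, so the conflict does not touch it.

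**The case against.** The strongest reply is that nothing need go wrong in practice. Section 5.4 names the time points by visit label as well as by day, and section 3.1 defines the outcome by visit label alone. No rule in the article assigns or excludes assessments by day window. The identical numbers in all three places suggest a misplaced anchor phrase rather than a second schedule, and the headings of sections 4.5 and 4.6 both refer to skin grafting. An analyst who uses whatever was recorded as visit 3 and visit 4 loses nothing.

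Most of this stands, and it rules out two stronger readings. A reader might infer that the plan throws away every on-schedule primary assessment. It does not say so; that would follow only if windows were built literally from section 5.4. A reader might also infer that graft ages are bound to be mixed. That requires time coded as days since visit 1, which the possible random slope permits but section 5.4 does not state.

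The comparison of arms is also largely protected. Each patient carries both treatments (4.3), both areas receive the same processed graft (2.6), and the plan describes one visit 2 per patient. A wrong anchor shifts both areas equally and does not by itself favour either arm.

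What does not stand is that the point is therefore harmless detail to be left for later. The article states explicit windows in both places and they exclude each other, so a later analysis plan could inherit either. Correcting the anchor phrase alone would also leave visit 1 listed as a time point for an outcome that does not yet exist.

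**Conclusion.** The contradiction holds on the document's own figures. Section 5.4 misstates when the primary endpoint is observed: days 4–6 and 12–14 from visit 1, against 7–20 and 15–28 under the visit plan, with no overlap for any permitted grafting day. It also includes visit 1, where graft take cannot be measured. This is a wrong rule in the primary analysis section, and it should be corrected before the analysis is programmed.

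The practical harm is conditional on someone building windows or numeric time from that wording. No bias in the comparison of arms at a given visit has been shown. That judgement rests on both areas in a patient being grafted at the same visit 2.

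The visit 5 part is minor. It is an ambiguity of anchor, and it would be loose wording only if postoperative was meant to refer to dressing application; section 2.6 points to grafting instead. A reader might infer that the 92-day duration is an error. The documents do not support that, because the figure follows from the application anchor and lies inside both possible windows.

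**What to change.** 1. In section 5.4, reconcile the time points with the visit plan: define those for graft take as visit 3 and visit 4 by label, with the windows of sections 4.5 and 4.6, and delete the count from intervention start.
2. State that time point enters the model as a categorical visit factor, not as days since visit 1. Any per-subject slope for time then becomes a per-subject difference between the two visits.
3. In the same sentence, remove visit 1 as an inference time point for graft take. This agrees with section 3.1, which lists only visits 3 and 4.
4. Minor: reconcile sections 2.1, 3.2 and 4.7 (heading and body) to one stated anchor for visit 5, and check that the total duration is described from that anchor with its window.

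The cost of items 1–3 is wording only. What is measured at visits 3 and 4 does not change, and neither does the sample size. Item 4 needs a decision by the investigators on what was intended.

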### Hypothesis

5.1

The null hypothesis of this trial is that amnion and skin allograft lead to the same amount of skin graft percentage take. The investigated alternative hypothesis is that the amnion allograft leads to a greater proportion of skin graft percentage take than the skin allograft.

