### Determination of sample size

5.2

A number of 30 patients was estimated to be required for the trial to have a 90% power to show an absolute difference of 5% points in wound healing at a two-sided alpha level of 0.01, given a paired design with both amnion and skin allograft applied to the same patient, and assuming a wound healing standard deviation of 6.7% points [Muhammadi et al. Burns 2012] [1].

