### Statistical criteria for termination of trial

5.3

The pre-planned study size of 30 patients is final, no interruption of the trial based on statistical criteria is planned.

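### The sample size assumes a two-sided alpha of 0.01, but the analysis section declares significance at p < 0.05, so one result can fail under one section and succeed under the other

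*Protocol article*

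**What the plan says.** Section 5.2 (Determination of sample size) justifies 30 patients by a calculation for a within-patient comparison of the two dressings. The SD enters as "assuming a wound healing standard deviation of 6.7% points", and the significance level is given in the words "at a two-sided alpha level of 0.01". The target is 90% power for a difference of 5 points.

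Section 5.4 (Planned analysis) describes a linear mixed effects model for the primary outcome, with Satterthwaite p values and no threshold in that paragraph. The next paragraph names the tests for population characteristics and then states: "A two-sided p < 0.05 was considered statistically significant". The sentence after it sets the reporting convention: "Values will be given as means and 95% confidence intervals or counts and (percentages) as appropriate".

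Section 5.1 (Hypothesis) sets out the claim to be tested, "The investigated alternative hypothesis is that the amnion allograft leads to a greater proportion of skin graft percentage take than the skin allograft", without an alpha. Section 5.3 fixes the size: "The pre-planned study size of 30 patients is final, no interruption of the trial based on statistical criteria is planned". No section reserves 0.01 for the primary outcome, and none mentions a multiplicity adjustment or another reason for two levels.

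**The concern.** The alpha in a sample size calculation is normally the level at which the primary hypothesis will be judged; the power statement has no meaning without it. Here the two sections give different levels and the article does not say which governs. Two things are at stake.

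- **The success criterion.** A primary p value between 0.01 and 0.05 is negative by the design section and positive by the analysis section. Unless this is settled beforehand, the choice can be made once the p value is known.
- **The stated operating characteristics.** If 0.05 governs, the nominal type I error of the primary test is five times the design value, and 90% is not the power of the test that will be used.

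**Working it through.** **Inputs.** From section 5.2: difference 5 points, SD 6.7 points, power 90%, two-sided alpha 0.01, paired design, n = 30. From section 5.4: two-sided threshold 0.05.

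**Assumptions.** Section 5.2 does not say whether 6.7 is the SD of the paired difference or of a single wound. I first take it as the SD of the difference. The mixed model is approximated by a paired t-test.

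**Step 1: reproduce the plan's figure.** The noncentrality parameter is (5 / 6.7) × √30 = 4.09 on 29 df.

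- At two-sided 0.01 the critical t is 2.756 and the noncentral t gives power 89.9% at n = 30; 31 patients are needed to pass 90%. The stated design reproduces.
- The normal approximation at 0.01 is [6.7 × (2.576 + 1.282) / 5]² = 26.7, so 27 patients. The t-based calculation is the one that comes close to 30.

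**Step 2: the same inputs at 0.05.** The critical t is 2.045. Power at n = 30 is 97.7%, and 21 patients are enough for 90% (19 by the normal approximation). On this reading of the SD, 30 patients follow from 0.01 and not from 0.05, so 0.01 does not look like a slip.

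**Step 3: the range of conflicting results.** The smallest significant observed difference is t × 6.7 / √30 = t × 1.223.

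- At 0.01: 2.756 × 1.223 = 3.37 points.
- At 0.05: 2.045 × 1.223 = 2.50 points.

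If the observed SD of differences is 6.7, an observed difference between 2.50 and 3.37 points passes under 5.4 and fails under 5.2.

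**Step 4: how often a trial lands there** (power at 0.05 minus power at 0.01, n = 30).

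| True difference (points) | Significant at 0.01 | Significant at 0.05 | In between |
|---|---|---|---|
| 0 | 1.0% | 5.0% | 4.0% |
| 2 | 15.1% | 35.3% | 20.2% |
| 3 | 39.6% | 65.9% | 26.3% |
| 5 | 89.9% | 97.7% | 7.8% |

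The first row is simply 0.05 minus 0.01.

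**Step 5: if 6.7 is the SD of one wound.** The SD of the difference is then 6.7 × √[2(1 − ρ)], where the within-patient correlation ρ is an assumption because the article gives none.

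| Assumed ρ | Power at 0.01, n = 30 | Power at 0.05, n = 30 | n for 90% at 0.01 | n for 90% at 0.05 |
|---|---|---|---|---|
| 0 | 55.9% | 79.8% | 57 | 40 |
| 0.3 | 75.2% | 91.6% | 41 | 29 |
| 0.5 | 89.9% | 97.7% | 31 | 21 |
| 0.7 | 99.2% | 99.9% | 20 | 14 |

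At ρ = 0 the SD of the difference is 9.48 and the conflicting range moves to 3.54 to 4.77 points. At ρ = 0.3 a calculation at 0.05 would give 29 patients, close to 30, but section 5.2 states 0.01 and no correlation. Whatever the SD means, the two thresholds still disagree.

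**The case against.** **The 0.05 sentence may cover only population characteristics.** It comes directly after the tests for those comparisons, in a separate paragraph from the mixed model, and its past tense suggests stock wording. This reading is possible but strained: the sentence is worded generally, sits among general statements on reporting and software, and is the only threshold in section 5.4. If the narrow reading were intended, section 5.4 would give the primary test no threshold at all, and the text would still need a correction.

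**Section 5.2 gives an alpha for sizing, not a rule for declaring success.** A sponsor may size at a stricter level than it tests at, and 5% two-sided is a conventional level. This is fair, and the mismatch does not push the error rate beyond convention. But the article does not say this was the intent. If it was, the 90% in section 5.2 is not the power of the planned test.

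**The figures depend on an SD that is not fully defined and on a paired t-test in place of the mixed model.** This stands. The boundaries and the 97.7% are conditional, as Step 5 shows, and should not be put into the protocol without that condition.

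**Nothing about design or data collection changes.** Also true. That makes the correction cheap; it does not make the success rule clear.

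**Conclusion.** The concern holds. Sections 5.2 and 5.4 give two different significance levels, and nothing in the article says which one decides the primary claim. This is a contradiction in the text as written, not detail left to another document.

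With 6.7 points as the SD of the paired difference and a paired t-test standing in for the mixed model, the conflict covers observed differences from 2.50 to 3.37 points. A trial falls there with probability 4.0% under the null, 26.3% at a true difference of 3 points and 7.8% at 5 points. The nominal type I error of a single test is 5% rather than 1% if section 5.4 governs, and power for 5 points is 97.7% rather than about 90%. The location of the range and the power depend on the meaning of the SD; the contradiction does not. It needs correcting because it determines whether the trial's main claim succeeds.

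**What to change.** Name one two-sided alpha for the primary contrast and use it in both sections.

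- **Keep 0.01.** State in section 5.4 that the amnion versus allograft contrast on graft take is tested at two-sided 0.01 and reported with a 99% confidence interval, which may stand beside the 95% one. State that 0.05 is a nominal level for all other comparisons. Thirty patients and about 90% power then stand on the SD-of-difference reading.
- **Or adopt 0.05.** Restate section 5.2 with alpha 0.05 and its power at n = 30: about 98% if 6.7 is the SD of the paired difference, otherwise the value for the stated per-wound SD and an assumed correlation.

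In either case, say in section 5.2 which SD the 6.7 is. Keeping 0.01 is the smaller change, since the sample size already allows for it.

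The cost is wording only: no change to the number of patients, the visits or the data collected. The price of 0.01 is a stricter bar for the primary claim. The change should be made and dated before the statistician's concealed allocation is broken.

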### Monitoring

5.5

Monitoring visits at the investigator's site prior to the start and during the course of the study will help to follow up the progress of the clinical study, to assure utmost accuracy of the data and to detect possible errors at an early time point. All original data including all patient files, progress notes and copies of laboratory and medical test results will be available for monitoring. The monitor will review all or a part of the eCRFs and written informed consents. The accuracy of the data will be verified by reviewing the above referenced documents. The investigator's site will collaborate with the Clinical Trials Center (CTC) of the University Hospital Zurich to ensure monitoring.

## Discussion

6

The treatment algorithm after burn injuries includes early removal of avital tissue in burn wounds to ensure optimal healing responses [40]. Surgical or enzymatic debridement are feasible and safe approaches to remove the necrotic tissue consequently needing coverage by wound dressings [[40], [41], [42]]. Advanced wound dressings have become a crucial aspect of burn care with a wide range of available dressings with diverse features [43,44]. The ongoing pursuit of the ideal burn wound dressing has led to experiments aimed at optimizing unwanted sequalae, such as infections or delayed re-epithelialization [43,45]. In these experiments the use of hydrogels, honey-based dressing, vacuum therapy, acellular fish skin graft and tissue-engineered constructs, and many more have aimed at challenging split skin grafting as the mainstay of treatment in burn injuries [46].

The use of amniotic membranes in burn treatment dates back as far as 1912 [28]. Since then, numerous studies have been able to explore the beneficial effects of using amniotic membranes as burn wound dressings, leading to an acceleration of the healing process and aiding in the reduction of bacterial colonization of these critical wounds [[29], [30], [31], [32], [33]]. The summative evidence on advantageous effects of treating burns with amniotic membranes have a wide range: lower rates of infection, a significant reduction in pain before and after dressing changes, reduction of hypertrophic scar formation, shorter duration of skin graft take, reduction in burn wound healing time, a reduction of needed dressing changes, a reduction in itching experienced and importantly a low immunogenicity [1,2,4,14,29,31,[47], [48], [49], [50]]. In terms of clinical application, the easy handling, light weight and elasticity give it ideal properties for the use even in complex anatomical areas [4].

Main possible adverse effects are concerning the transmission of infectious diseases such as human immunodeficiency virus, hepatitis C virus, or hepatitis B virus [1,14]. There have been no reports of disease transmissions up until now, given the rigorous screening methods when harvesting the amniotic membranes [30]. Therefore, we expect minimal risks for patients participating in this study since the use of amniotic membrane has proven to be a safe transplant product and we intend to fulfill all necessary safety requirements of Good Manufacturing Practice - as specified in chapters 5, 8 and 18 of the “Guide to the quality and safety of tissues and cells for human application” by the European Directorate for the Quality of Medicines & Healthcare - to avoid any microbiological contamination [51,52].

Reliable additional information on the treatment of burn wounds with amniotic membranes is needed. The knowledge gained in this project may help to routinely include this advantageous modern concept of biological dressings in clinical practice. Moreover, our study will add to the already existing body of knowledge when using amniotic membranes, which have been harvested and processed in an in-hospital supply chain. Current studies have either used commercially available dehydrated amniotic membranes, or as we suggest here, have harvested and processed the membranes in hospital [14,[53], [54], [55]].

The purpose of this study is to use human amniotic membranes, manufactured in our hospital eye bank laboratory, as an allogenic biological dressing after enzymatic debridement in mixed or deep partial thickness burn wounds. Our long-term goal is the implementation of the treatment with amniotic membranes as a standard of care with an in-hospital supply chain. We believe that this will provide a clinically and economically alternative to allogenic skin grafts.

